#### Body satisfaction and self-perception

To assess attitudes and perceptions of gender and body among individuals with DSD, no published standardised instrument was appropriate for our research questions. Thus, twelve items were developed to evaluate the own satisfaction or perceived satisfaction of the child’s body, gender, and maleness and femaleness, respectively. The responses can be chosen between very satisfied and very dissatisfied and ‘no answer possible’. For the questions about maleness and femaleness, the respondents can classify on a 5-point Likert scale between very male and very female, ‘sometimes like this, sometimes like that’ or ‘I don’t know’. Self-esteem and shame are asked in three questions about the persons and the feelings associated with talking about the diagnosis and the body.

The Body Image Scale (BIS) is used to evaluate the satisfaction with body parts like primary gender, secondary gender, and hormonally unresponsive attributes [46]. It comprises 30 body features that the respondent is asked to rate on a 5-point Likert scale between very satisfied and very dissatisfied. In the original version, the respondent was asked about the desire to change a body part by surgery, but this was beyond the scope of the present study and has therefore been omitted [46]. The instrument showed a consistent reproducibility of the scores [46]. The outcome measure is used in a German translation, that was already applied to a German sample of adolescents with DSD [41]. In the present study, the BIS is used for all participants between 12 and 24 years.

#### Diagnosis-specific knowledge

To evaluate the improvement of diagnosis-specific knowledge, self-constructed multiple-choice items were developed. The questionnaire comprises six items for each diagnosis, for both children and parents, but with different perspectives and levels of difficulty. The same questions are asked before and then at follow-up after three and six month after the education programme. For statistical evaluation, the individual items are added up to an overall score.

#### Satisfaction with programme

The questionnaire for the evaluation of the satisfaction with the education programme is based on an instrument, which was originally developed for the assessment of patient satisfaction with inpatient care [47]. Psychometric properties were evaluated as high, with a Cronbach’s alpha between 0.88 and 0.92 [48]. For programme evaluation, the items were adapted and further questions were added. A similar adapted version was already used in the evaluation of an asthma-specific ModuS programme [27]. Basic quality requirements of patient education programmes were discussed and transformed into items of the questionnaire [49]. Finally, ten questions with a 4-point Likert scale and two open-ended questions are set for the survey immediately after the training for parents and adults. To evaluate children’s and adolescents’ satisfaction, a shorter version with one item on general satisfaction, two open-ended questions, and four items with a 5-point smiley scale is used.

### Data management

For the online-based data assessment we use the remote data capture system REDCap. Separate questionnaires were programmed for the target groups based on age and diagnostic groups. Before the study centres started the field work, they were trained in using REDCap by the central data management following a standardised training scheme.

The participant information form contains all the relevant information used to assign the diagnosis- and target group-specific questionnaires in the surveys. Family relationships are also assigned via this form, so that the responses of the parents can be linked to those of the associated children. The study included the following 4 groups: (i) children aged 6 to 13 years, (ii) adolescents aged 14 to 17 years, (iii) young adults aged 18 to 24 years (all groups with links to the corresponding parental questionnaires), (iv) parents of children newly diagnosed within the last two years. Baseline and follow-up assessments were separately programmed for each age group. Access codes for baseline and 3 follow-up assessments were generated for each participant and included the individual participant information.

Complex alpha-numeric pseudonyms are used as links between diagnosis- and age group-specific questionnaires. The pseudonyms were generated at the central data management. A list with a sufficient number of pseudonyms together with guidelines for documenting the use of them was sent to each study centre before the recruitment started.

The following quality assurance tasks are important in this project phase on the part of the central data management:

(i) Checking the family assignments for correctness, if necessary submit queries to the study centre. This ensures the correct assignment of questionnaires to the different assessment time points, but it is also essential for future evaluations in terms of linking questionnaire responses of parents with those of their children.

(ii) Verifying that questionnaires have been completed. A message regarding the completeness of the questionnaires is also included in the participant information. This was subsequently added by the central data management to help the local study nurses keeping track.

During the course of the project, it is important to keep a close communication between the central data management and the study centres to identify sources of error early and to correct them quickly, if possible.

Personal data from the qualitative interviews (e.g. audios) are only stored digitally with special access authorisation. Audios, complete transcripts or other person-identifying data are only transport encrypted, e.g., with a VeraCrypt container. Only pseudonymised data will be analysed.

### Statistical methods

Descriptive statistics will be presented for the subsamples children (6–13 years), adolescents (14–17 years), young adults (18–24 years), and parents separately. Categorical variables will be reported as absolute and relative frequencies (with 95% confidence interval), normal distributed metric variables as mean and standard deviation, and skewed variables as median with interquartile range.

Pre-post comparisons (before vs. after training) will be conducted with statistical tests for paired samples (single-factor ANOVA with repeated measures, one-sample t-test, McNemar test) separately for children, adolescents, young adults, and parents. All tests are two-sided with a significance level of 0.05. However, *p*-values are considered exploratory, without adjustment for multiple testing. Missing data will not be imputed. No interim analyses are planned. A statistical analysis plan will be prepared prior to data analysis.

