### Evaluation

The education programme will be quantitatively and qualitatively evaluated by means of standardised questionnaires, interviews and participating observations. For the quantitative evaluation, patients and their relatives who participate in the education programme are requested to fulfil online questionnaires at four time points: at baseline before participation in the education programme (t0), immediately after participation in the education programme (t1), and at a follow-up 3 months (t2) and 6 months (t3) after participation. Table 3 shows the questionnaires used at the different time points in the evaluation.

**Table 3 Tab3:** Questionnaires of the quantitative evaluation of the study

Subgroup of sample	Time point	Standardised questionnaires	Self-constructed items
Parents of children under 6 years (includes parents of newly diagnosed children under 6 years)	T0, T2, T3	Cantril ladder, WHO-5	Sociodemographic data, diagnosis-specific items, social support, gender, maleness and femaleness, shame, self-esteem, disease burden and general coping, knowledge
Parents of children older than 6 years (includes parents of newly diagnosed children older than 6 years)	T0, T2, T3	Cantril ladder, KINDL-R parents, WHO-5	Sociodemographic data, diagnosis-specific items, social support, gender, maleness and femaleness, shame, self-esteem, disease burden and general coping, knowledge
Children 6–13 years	T0, T2, T3	Cantril ladder, KINDL-R (version 7–13 years), CODI (for children older than 7 years), BIS (for children older than 12 years)	Sociodemographic data, diagnosis-specific items, social support, gender, maleness and femaleness, shame, self-esteem, disease burden and general coping, knowledge
Adolescents 14–17 years	T0, T2, T3	Cantril ladder, KINDL-R (version 14–17 years), CODI, BIS	Sociodemographic data, diagnosis-specific items, social support, gender, maleness and femaleness, shame, self-esteem, disease burden and general coping, knowledge
Young adults 18–14 years	T0, T2, T3	Cantril ladder, WHO-5, BIS	Sociodemographic data, diagnosis-specific items, social support, gender, maleness and femaleness, shame, self-esteem, disease burden and general coping, knowledge
Children and adolescents 6–17 years	T1		satisfaction with programme, short version
Young adults 18–14 years	T1	Adapted ZUF-8	satisfaction with education
Parents of all children and adolescents	T1	Adapted ZUF-8	satisfaction with education

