As a first result of the Empower-DSD study, a specific DSD patient education programme is developed. For each diagnosis and for each age group (children, adolescents and young adults, parents/carers), a separate curriculum specifies learning objectives, content, and learning methods. Each manual includes an exemplary schedule for the implementation of the education programme. According to the manuals, the advanced DSD training academy was established and a total of 56 professionals, e.g., medical doctors, psychologists, social workers or medical assistants, were qualified to conduct the educational programme in the different study centres. The education programme is offered in groups separated by age and diagnosis. Usually, an education course takes two days with a total of 12–14 lessons of 45 min each. The courses of the children/adolescents take place simultaneously with the training of parents/carers. The groups are limited to 4–8 families. Furthermore, peer counsellors are an integral part of the educational programme. At each date, a peer from the cooperating patient support group is available to talk about the peer’s own experience in daily life with the diagnosis and to answer questions. Up to this day, a total of 336 subjects have been enrolled in the study and took part in the educational programme. Meanwhile, there have already been educational events provided for each diagnosis at least once. After each event, a feedback discussion takes place and the trainers of a centre fulfil a structured feedback form including information on organisation, methods, positive and negative training experiences to improve the quality of the educational programme. In order to benefit from the experiences of the other study centres, regular online meetings are held between the trainers.

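### The planned pre-post tests treat participants as independent although the programme is taught in shared courses; a course-clustered variance is recommended

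*Protocol article*

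**What the plan says.** All places are in the protocol article.

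- **Statistical methods.** On the effect analysis: "Pre-post comparisons (before vs. after training) will be conducted with statistical tests for paired samples (single-factor ANOVA with repeated measures, one-sample t-test, McNemar test"). Each of the three age groups of patients, and the parents, is tested on its own. On the error level: "All tests are two-sided with a significance level of 0.05". The p-values "are considered exploratory, without adjustment for multiple testing". The only confidence intervals named are for frequencies: "Categorical variables will be reported as absolute and relative frequencies (with 95% confidence interval"). A statistical analysis plan is announced.
- **Discussion.** Courses are formed by age and diagnosis, parents are taught in parallel with their children, and a peer counsellor attends each date. On size: "The groups are limited to 4–8 families".
- **Evaluation.** On who responds: "patients and their relatives who participate in the education programme are requested to fulfil online questionnaires". No limit of one caregiver per child is stated.
- **Data management.** Family relationships are recorded "so that the responses of the parents can be linked to those of the associated children". The Statistical methods section makes no use of these links.

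Neither Sample size nor Statistical methods mentions a course, family or centre effect, a design effect, or a variance that allows for clustering.

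**The concern.** Members of one course share the trainers, the peer, the date and the group itself. The Discussion presents interaction within the group as a main strength of the programme, and it says trainers use feedback after each event to improve delivery. So the change from baseline, and not only the level, may well be more alike within a course than between courses. Taking each person's difference removes stable course differences in level but not a shared course effect on change.

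Because courses are formed by age and diagnosis, members of a course fall largely into the same age-group test. In the parent test, two caregivers of one child would add a family correlation. The one-sample t-test, single-factor repeated-measures ANOVA and McNemar test ignore both.

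The study has no control group, so the pre-post change and its uncertainty carry the quantitative evidence of effect. The mean change itself is not the problem; its stated precision is.

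**Working it through.** **1. The plan's own figure.** Inputs from Sample size: n = 300, standardised paired difference 0.4, two-sided 0.05. With the noncentral t distribution (299 degrees of freedom, noncentrality 0.4 × √300 = 6.93) the power is above 99.99%. The stated figure of over 95% is therefore reproduced as a lower bound. A power of 95% needs 84 independent participants.

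**2. Formulas for clustering.** With m respondents per course in one test and ICC the correlation of change scores within a course:

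- design effect DE = 1 + (m − 1) × ICC
- true SE / naive SE = √DE
- actual error of a nominal 5% test = 2 × [1 − Φ(1.96/√DE)]

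The course size of 4–8 comes from the Discussion, taking one respondent per family in a given test. The ICC is not in the article; 0.01–0.20 is an assumed range.

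| m | ICC | DE | true SE / naive SE | actual error |
|---|---|---|---|---|
| 4 | 0.01 | 1.03 | 1.015 | 5.35% |
| 4 | 0.05 | 1.15 | 1.07 | 6.8% |
| 4 | 0.10 | 1.30 | 1.14 | 8.6% |
| 4 | 0.20 | 1.60 | 1.26 | 12.1% |
| 8 | 0.01 | 1.07 | 1.034 | 5.8% |
| 8 | 0.05 | 1.35 | 1.16 | 9.2% |
| 8 | 0.10 | 1.70 | 1.30 | 13.3% |
| 8 | 0.20 | 2.40 | 1.55 | 20.6% |

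The ratio says how much larger the true SE is than the naive one. Seen from the other side, at DE = 2.40 the naive SE is too small by 1 − 1/1.549 = 35%.

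**3. Courses that split across tests.** Adolescents and young adults share a curriculum but are tested separately (14–17 and 18–24 years). If only 2 members of a course enter one test, DE at ICC 0.20 is 1 + 1 × 0.20 = 1.20 and the actual error is 7.4%.

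**4. Parents, upper scenario.** Assume 6 families per course, two responding caregivers in every family, a within-family correlation of change ρ_f and a correlation between families of one course ρ_c. Each parent then has 1 partner and 10 other course members:

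DE = 1 + ρ_f + 10 × ρ_c

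- ρ_f = 0.3, ρ_c = 0.05: DE = 1 + 0.3 + 0.5 = 1.8, actual error 14.4%
- ρ_f = 0.5, ρ_c = 0.10: DE = 1 + 0.5 + 1.0 = 2.5, actual error 21.5%

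**5. Effect on the power statement.** At m = 8 and ICC 0.20 the effective sample size is 300/2.40 = 125 and the power is 99.3%. It would fall below 95% only if DE exceeded 300/84, about 3.6, which none of the scenarios above reaches.

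**The case against.** **Exploratory status.** The study is called explorative and the p-values exploratory, so no confirmatory error rate is claimed. This lowers the consequence and settles the severity. It does not correct a standard error: an exploratory p-value should still reflect the design.

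**The analysis plan to come.** The article is condensed, and a variance that allows for clustering could be specified in the announced plan. That is a good place to make the change. But the article does not leave the method open: it names tests that assume independent persons, and an analysis plan that follows it would inherit the problem.

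**Unknown size.** This stands. At an ICC of 0.01 the actual error is only 5.35–5.8%. The parent figures need two responding caregivers in every family, and the article does not say how often that happens. Splitting of courses and missing follow-up, which is not imputed, reduce the number per course in a test.

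**Stronger readings the article does not support.**

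- A reader might infer that the sample size is inadequate. It is not: the stated power holds in every scenario above.
- A reader might take 14–22% as the expected error in the parent test. It is an upper scenario.
- A reader might think parent–child correlation distorts the tests. Parents and patients are tested separately, so it enters no single test.
- A reader might conclude that the confidence interval of the mean change is wrong as planned. Intervals are named only for relative frequencies, and the evaluation also rests on the qualitative part.
- A reader might infer that course membership is not recorded. The article does not say so.

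**Conclusion.** The point holds as a conditional one. The named tests treat persons as independent, while delivery in shared courses, and possibly several respondents per family, makes correlated changes plausible. Any positive correlation of change within courses or families makes the standard errors too small and the p-values too optimistic.

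The direction follows from the design; the size rests on the assumed ICC. It runs from negligible at ICC 0.01 to a true SE 55% larger than the naive one at ICC 0.20 with 8 per course. It is smaller where courses split across age groups, and the figures for parents depend on the further assumptions listed with them.

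Because the analyses are exploratory and the power statement survives, this is a recommended improvement and not a must-fix.

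**What to change.** Keep the paired mean change in each group as the estimate, and compute its variance with a small-sample cluster-robust method (CR2 with Satterthwaite degrees of freedom) clustered on the course. Families lie within courses, so this covers the family correlation too.

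Alternatively, fit a mixed model per group with a course-by-time random effect and, for parents, a family-by-time random effect. Random intercepts for course or family alone are not enough, because they cancel from the change score; main effects of diagnosis or centre cancel in the same way and do not address the point.

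For binary outcomes, replace the plain McNemar test by the corresponding cluster-adjusted method. Make sure the course identifier is in the analysis data set alongside the family link.

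The cost is slightly wider intervals, some wording in the analysis plan and a little more analysis work. No additional participants are needed.

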### Sample and recruitment

The modular education programme is conducted for children and young adults aged 6–24 years with DSD and their parents, as well as for families with a child newly diagnosed with DSD within the last two years. The potential study participants will be contacted by the study centres and their cooperating institutions, such as regional endocrinologists, patient support groups or other hospitals. The recruitment includes e-mail or phone contact after initial information by the physician during the consultation, information by a project flyer distributed by one of the partners or information from the Empower-DSD website (https://empower-dsd.charite.de). Additionally, professionals and peers who work with or consult patients with DSD and their families and who are involved in the development of the Empower-DSD concepts are recruited for the qualitative evaluation of the study. The inclusion criteria are presented in Table 2. Subjects are excluded if informed consent is missing, if they are participating in another study addressing patient education related to DSD or if a language barrier disables participants from taking part in the programme.

**Table 2 Tab2:** Inclusion criteria

Inclusion criteria
Patients with congenital adrenal hyperplasia (CAH), Klinefelter syndrome, Turner syndrome, XX-/XY-DSD including MRKH
Confirmation of diagnosis by chromosomal analysis, genetic test result, laboratory test or clinical examination
Children between 8–13 years (according to their cognitive development from the age of 6 years)
adolescents/young adults between 14–24 years
Parents/ caregivers of children or adolescents with DSD newly diagnosed in the last two years
Professionals who provide the patient education programme or have been involved in its development
Peers who participate in the patient education programme as peer counsellors or were involved in its development process
Written informed consent is available from patients (6 years and older), parents/ caregivers, peers, and professionals

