### Sample size

The study follows an explorative approach and aims to include as many cases as possible in all five centres during the field phase. A sample size of 300 participants provides a power of over 95% with moderate effects of the education programme (standardised difference of paired means of 0.4) with an exploratory significance level of 0.05 (two-sided). Due to an expected drop-out of less than 15%, the aim is to recruit 350 children and 350 adolescents/young adults for the study. This lost-to-follow-up is considered realistic from previous paediatric research projects, because the subjects in the current study will have frequent consultations with the team of the department of endocrinology due to their diagnosis. Approximately 160 *newly* diagnosed cases are expected to occur in all centres together during the observation period based on previous year’s occurrence. Therefore, a participation of 100 families with newly diagnosed children in the study seems realistic. To ensure the participation of the families until the last follow-up, a strict reminder management is carried out and gift cards are awarded among all participants who have completed all questionnaires.

Regarding the qualitative evaluation, we plan to conduct approximately 50 semi-structured interviews with patients, parents, professionals, and peers taking part or working in the education programme. Based on the explorative assumptions of qualitative research, the number or content of the interviews can be adjusted until theoretical saturation is reached.

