#### Life satisfaction and well-being

To assess general life satisfaction and well-being, the Cantril ladder and the WHO-5 are used. The Cantril ladder is a visual scale on which subjective life satisfaction is marked on ladder levels between 0 and 10 [33]. The highest level represents the best possible life and the lowest level the worst possible life. The respondent should mark the personal life satisfaction of the present moment. The original version of the Cantril ladder was developed for the use in adult populations [34, 35]. The reliability and reproducibility have been confirmed for several life satisfaction scales. They reflect different living conditions and make a valid statement regarding future behaviour [36]. For samples with children and adolescents, an adapted version without an initial imagination of the best and worst life has been developed for the Health Behaviour in School-aged Children (HBSC) studies [37]. Good validity and reliability for this adapted version has been confirmed by several studies [33, 34]. In the present study, the adapted version for children, adolescents, young adults as well as for parents is used to reflect on one's own life satisfaction.

The WHO-5 instrument is a generic assessment of psychological well-being, which is widely used all over the world and translated into 31 languages. Psychological well-being is an essential dimension of HRQoL [38]. The WHO-5 has a good psychological and clinical validity across different settings and samples. In the context of chronic diseases and diagnostic screening, it is even able to reveal depression [39]. In this study, the instrument is used for the adult sample, including parents and patients older than 18 years as a main outcome measure.

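### Ages 14–17 and 18–24 are tested only separately; on the instruments both ages answer, one combined 14–24 estimate with an age-by-time difference should be added

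*Protocol article*

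**What the plan says.** The Statistical methods section describes the "subsamples children (6–13 years), adolescents (14–17 years), young adults (18–24 years), and parents separately" and runs the paired pre-post tests "separately for children, adolescents, young adults, and parents". The rule is the same for every outcome, and no combined 14–24 result is named.

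Three other places treat the two ages as one group:
- **Sample and recruitment, Table 2:** one eligibility band, "adolescents/young adults between 14–24 years".
- **Sample size:** "the aim is to recruit 350 children and 350 adolescents/young adults for the study".
- **Discussion:** "for each age group (children, adolescents and young adults, parents/carers), a separate curriculum specifies learning objectives, content, and learning methods", written for each diagnosis.

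On measurement, Table 3 gives the Cantril ladder and the BIS to both ages and lists the same self-constructed domains for both. (The young-adult row is printed as 18–14 and is read here as 18–24.) The Instruments text agrees. For the BIS: "In the present study, the BIS is used for all participants between 12 and 24 years". For the Cantril ladder: "the adapted version for children, adolescents, young adults as well as for parents is used". By contrast, KINDL-R and CODI are listed for patients only up to 17, and among patients WHO-5 is given only to young adults.

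The Data management section lists adolescents and young adults as two separate study groups.

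**The concern.** For this age range the programme has one curriculum per diagnosis, and one number was set for recruitment. The planned analysis gives two smaller results and no estimate for the group as recruited and taught. Where the scale differs between the ages, that cannot be avoided. Where the scale is the same, two things are lost:
- **Precision.** A modest change shared by both ages is estimated with wider intervals and may be missed in one or both halves.
- **Protection against a false age contrast.** One significant and one non-significant half is easily read as an effect confined to one age. The section plans no age-by-time comparison to test that reading.

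**Working it through.** **1. The plan's own figures.** Inputs from the Sample size section: n = 300, standardised paired difference d = 0.4, two-sided level 0.05, drop-out under 15%. Power of a paired t-test comes from the noncentral t with n − 1 degrees of freedom and noncentrality d√n.
- d√n = 0.4 × √300 = 6.93, so power exceeds 99.99%. This agrees with the stated power of over 95%.
- 350 × 0.85 = 297.5 completers, close to 300. The power statement therefore fits the 14–24 band as a whole.

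**2. An assumed age split.** The article gives no breakdown within 14–24. For illustration, 300 completers are spread evenly over the 11 year-bands from 14 to 24:
- 14–17: 300 × 4/11 = 109
- 18–24: 300 × 7/11 = 191

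**3. Precision and power for one pre-post change.** The 95% half-width in SD units of the change is t(0.975, n − 1)/√n.

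| Group | n | Half-width | Power at 0.2 SD | Power at 0.4 SD |
|---|---|---|---|---|
| 14–24 combined | 300 | 1.968/17.32 = 0.114 | 93.2% | >99.9% |
| 14–17 | 109 | 1.982/10.44 = 0.190 | 54.4% | 98.5% |
| 18–24 | 191 | 1.973/13.82 = 0.143 | 78.5% | >99.9% |

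**4. Other splits.**
- With an even 150/150 split, each half has a half-width of 0.161 SD, 68.2% power at 0.2 SD and 99.8% at 0.4 SD.
- At 0.4 SD, a stratum falls below 95% power only with fewer than 84 completers.
- With 100 completers in all (36/64 by the same age shares), power at 0.4 SD is 64.6% and 88.3%, against 97.7% combined. The figure of 100 is an assumption. The Discussion reports 336 subjects enrolled so far across the whole study, without an age breakdown.

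**5. Discordant halves.** Suppose both ages truly change by 0.2 SD. The chance that exactly one of the two tests is significant is p₁(1 − p₂) + p₂(1 − p₁):
- 109/191: 0.544 × 0.215 + 0.785 × 0.456 = 0.475, about 47%
- 150/150: 2 × 0.682 × 0.318 = 0.434, about 43%

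**6. The age-by-time difference.** With equal SDs of change its standard error is √(1/109 + 1/191) = 0.120 SD, so its 95% half-width is about 1.968 × 0.120 = 0.24 SD. It is imprecise, but it answers the question of whether the ages differ, which two separate p-values do not.

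**The case against.** The strongest case for the plan as written has five parts.

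- **The split follows the study's own groups and its main measurements.** Data management lists the two ages separately, with separately programmed assessments. KINDL-R, the primary instrument, stops at 17, and WHO-5 is a main outcome measure for adults. This stands, and it justifies keeping the stratified results. A reader might infer that pooling is missing on every outcome, or that the split itself is an error. The documents do not support that, because KINDL-R, CODI and WHO-5 cannot be pooled across age 18.
- **Power is adequate at the planned effect.** This stands. At 0.4 SD the 109/191 split keeps over 98% power in each half. A reader might infer that the split invalidates the sample size, and at the planned numbers it does not.
- **Few shared scales are named outcomes.** This stands in part. The Cantril ladder and the BIS are not in the article's lists of primary and secondary outcomes. For shame, burden and general coping, Table 3 shows the same domain labels but does not say that the items are identical. Knowledge is less certain still, since its versions are described only for children and parents.
- **Curricula also differ by diagnosis.** This is true, so a combined 14–24 figure averages over diagnoses. Each planned age stratum does so as well.
- **The tests are exploratory and an analysis plan is to follow.** That plan could add a combined result, so it would be wrong to infer that the programme will never get one. The article still fixes the unit of testing and names only the split. Wider intervals matter under any policy on p-values.

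**Conclusion.** The point holds in a limited form. The unit of analysis does not match the unit of recruitment and teaching for ages 14–24. On instruments answered at both ages, the plan gives up precision without need. Under the assumed 109/191 split, intervals are about 1.7 times (0.190/0.114) and 1.3 times (0.143/0.114) as wide as the combined one. For a 0.2 SD change, power near 93% falls to 54% and 79%, and discordant halves would be common even with no true age difference.

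The figures rest on an assumed age distribution, 300 completers, one pre-post contrast, and the same SD of change and the same true change in both ages. The primary outcome and the stated power are not affected.

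**What to change.** Keep the planned age-stratified results for all outcomes. In the statistical analysis plan, before data analysis, add one combined 14–24 pre-post estimate with its 95% interval for the Cantril ladder and the BIS. Include age group (14–17, 18–24) as a factor, and report the age-by-time difference with its interval. Extend this to self-constructed items such as shame, burden and general coping only after checking that wording and scoring are identical at both ages. Leave KINDL-R, CODI and WHO-5 separate. State that an age difference will be judged from the age-by-time interval and not from comparing two p-values.

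The cost is analysis-plan wording and a few table rows, with no new data or participants. The combined figure averages two age groups, which the retained stratified rows make visible.
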